#### Primary outcome

The primary outcome will be compared between treatment groups using survival analysis methods. A Cox proportional hazard model will be fitted if the assumptions of proportionality are met, and an adjusted HR with a 95% CI will be presented. The p value relating to the intervention group parameter as generated by the model will be presented. Kaplan-Meier survival curves will be constructed for visual presentation.

#### Secondary outcome

Secondary outcomes which are considered time-to-event outcomes (transplant-free survival at 6 weeks) will be analysed in the same manner as the primary outcome (with the exception of p value reporting). Secondary outcomes which are considered binary (eg, rebleeding, complications of cirrhosis and use of cross-over therapies) will be summarised using frequencies and percentages. A log binomial regression model will be fitted and results presented as adjusted risk ratios, risk differences and 95% CIs. Continuous outcomes (eg, Child-Pugh and MELD scores) will be reported using means and SD at each time point. A mixed effects repeated measures model will be fitted and results presented as mean differences and 95% CIs at the primary time points (6 and 12 months). Longitudinal plots of the mean scores over time by treatment group will be produced for visual inspection of the data.

#### Planned subgroup analyses

Subgroup analyses will be limited to the same variables used in the minimisation algorithm as described above and performed on the primary outcome only. The effects of these subgroups will be examined by including an intervention group by subgroup interaction parameter in the regression model, which will be presented alongside the effect estimate and 95% CI within subgroups. The results of subgroup analyses will be treated with caution and will be used for the purposes of hypothesis generation only.

#### Missing data and sensitivity analyses

Every attempt will be made to collect full follow-up data on all participants; it is thus anticipated that missing data will be minimal. Any participants with missing primary outcome data up to 12 months will be included in the primary analysis up to the point where their clinical status (mortality and transplant data) is last known (censored at this point), therefore no sensitivity analyses to assess the impact of missing data are proposed for the primary outcome. Full details of any other sensitivity analyses will be included in the statistical analysis plan.

### Economic evaluation

The economic evaluation will assess the cost-effectiveness of early TIPSS versus standard of care (SOC) by calculating the cost per life year gained and cost per QALY gained over 12 months and lifetime from an NHS and Personal Social Services perspective.

A within-trial cost-effectiveness analysis will be conducted based on the outcomes of cost per life year gained and cost per QALY estimated using EQ-5D-5L responses at baseline, 6 and 12 months.^29^ Healthcare resource use information will be prospectively collected through CRFs and at regular follow-up hospital appointments. Resources include the intervention (early TIPSS) and standard of care (endoscopic treatment, medications), rebleeding, liver failure and transplantation, follow-up care including outpatient visits, investigations (eg, endoscopy), inpatient stays, admission to intensive care unit, treatment of adverse events and other complications and readmissions. Mean costs and outcomes will be estimated for both trial arms and non-parametric bootstrapping will be used to estimate 95% CIs around differences in mean costs, EQ-5D-5L scores and QALYs. In the base case, where there is missing cost and outcome data, multiple imputation will be used. Imbalances in baseline variables such as EQ-5D-5L Score between trial arms will be controlled for using a regression approach. Incremental cost-effectiveness ratios will then be calculated. Cost-effectiveness acceptability curves (CEACs) will be used to plot the probability of each intervention being cost-effective at different thresholds of willingness to pay per additional unit of outcome.

If there is evidence from the trial that differences between early TIPSS and SOC exist in terms of liver transplantation and mortality as well as other outcomes that may have significant cost or outcome implications beyond the trial period, a Markov model-based economic evaluation will also be conducted over a lifetime time horizon with discounting of 3.5% for costs and outcomes. Clinical and economic evidence collected as part of the trial and other secondary sources will be used to parametrise the model. Deterministic and probabilistic sensitivity analyses will be conducted to explore the robustness of the results and CEACs presented. Value of information analysis will also be undertaken to investigate the value of, and the need for, further information on key uncertain model parameters.

All methods and analyses will be reported as recommended by the Consolidated Health Economic Evaluation Reporting Standards reporting guidelines and full details of the analysis will be included in the health economics analysis plan.^30^

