## Introduction

### Existing research and current practice

Liver disease is the fifth largest cause of death in the UK. There had been a five-fold increase in the development of cirrhosis in 35–55 year olds between 2003 and 2013, with 30 000–60 000 at risk or affected by liver cirrhosis. Approximately 50% of patients with cirrhosis develop varices, which equates to over 25 000 prevalent cases.^1^ Variceal bleeding has an inpatient mortality rate of 15% and 1-year mortality rate of up to 40%.^2^ Increased hospitalisation results in increased use of secondary care and substantial healthcare costs. Therefore, optimising the management of acute variceal bleeding (AVB) to minimise the risk of variceal rebleeding and improve survival are important clinical and economic goals.

Current clinical practice guidelines recommend endoscopic therapy with variceal band ligation (VBL) for treating acute oesophageal variceal bleeding or tissue adhesives or thrombin injection for acute gastric variceal bleeding in combination with drug therapy (terlipressin and antibiotics).^3 4^ Transjugular intrahepatic portosystemic stent–shunt (TIPSS) is recommended where these measures fail to control bleeding. This well-established emergency strategy is often referred to as ‘rescue’ or ‘salvage’ TIPSS therapy. However, although rescue TIPSS therapy controls variceal bleeding in over 90% of patients, the mortality can be as high as 36% at 6 weeks and 42% at 1 year.^5 6^ Patients with advanced cirrhosis and decompensation (Child-Pugh Score>13, lactate≥12 mmol/L and/or MELD Score≥30) have high levels of mortality and TIPSS in this patient group is likely to be futile.^5 7^

There has been much interest in TIPSS, not as a *rescue* therapy due to ongoing AVB but as an *early (ie, prophylactic or pre-emptive*) therapy in selected high-risk patients after initial control of bleeding with standard endoscopic and drug therapy. The risk of variceal rebleeding can be as high as 60%, with each variceal rebleeding episode associated with 20% mortality, particularly in the first 5 days following a bleed.^8^ Therefore, early interventions during the AVB episode are likely to have the greatest impact on outcomes.

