A meta-analysis of two RCTs and two observational studies demonstrated that early TIPSS is associated with reduced overall mortality compared with standard of care (OR 0.38, 95% CI: 0.17 to 0.83, p=0.02).^9 15 20–22^ The reduced mortality was only observed in patients with Child-Pugh C Score<14. There was significantly less rebleeding with early TIPSS without significant difference in hepatic encephalopathy. An individual patient data meta-analysis of 7 studies (3 RCTs and 4 observational studies) of 1327 patients showed 6-week and 1-year survival rates were significantly higher in the early TIPSS group than the standard of care group (93% vs 76.8% and 79% vs 62%, respectively, log-rank p<0.001).^10 18–23^ The improved outcomes of early TIPSS were seen in Child-Pugh B and C patients with active bleeding. Number of patients needed to treat to save one life was 4.23 (95% CI: 3.57 to 6.94). There were no significant differences with respect to hepatic encephalopathy. However, both randomised controlled and observational studies were included, and the authors concluded that further prospective studies were necessary. The same group updated this individual patient data meta-analysis,^24^ incorporating the UK RCT,^14^ although a multicentre French audit was not included.^16^ The results confirmed benefit of early TIPSS with improved survival of a similar magnitude in Child-Pugh Score 8–13 patients and in those with Child-Pugh B disease and active bleeding. Another meta-analysis included all four key RCTs,^10 14 20 21^ although it was not based on individual patient data.^25^ Analysis of these RCTs demonstrated no significant difference in mortality at 6 weeks (relative risk (RR) 0.33, 95% CI: 0.08 to 1.36) or at 1 year (RR 0.76, 95% CI: 0.51 to 1.14). The authors recommended a sufficiently powered RCT to answer this question.

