#### Secondary outcomes

Transplant-free survival at 6 weeks (post randomisation).Rebleeding (Rebleeding is defined as haematemesis and/or melena with either: (1) endoscopic evidence of variceal bleeding or stigmata of recent haemorrhage and at least a 2 g/L reduction in haemoglobin within 24 hours of admission or (2) massive upper gastrointestinal bleeding leading to death. The definition includes bleeding from banding ulceration.) (post randomisation):Early (less than or equal to 6 weeks).Late (greater than 6 weeks).Serious adverse events related to treatment (up to 12 months post randomisation).Other complications of cirrhosis (up to 12 months post randomisation; composite outcome and individual components):New onset ascites.New onset encephalopathy. (Hepatic encephalopathy will be assessed according to West Haven criteria as the most severe grade.^28^ The number of episodes of hepatic encephalopathy will be recorded in follow-up CRFs. Covert or minimal hepatic encephalopathy will be assessed using the animal naming test where less than 20 animals named in 1 min is highly suggestive of minimal or covert hepatic encephalopathy.^28^)Spontaneous bacterial peritonitis.Hepatocellular carcinoma.Any renal dysfunction.Child-Pugh Score at 6 and 12 months post randomisation.MELD Score at 6 and 12 months post randomisation.Cross-over therapies.Health-related quality of life (EQ-5D-5L) at 6 and 12 months post randomisation.Use of healthcare resources, costs and cost-effectiveness based on cost per quality-adjusted life-year (QALY) estimated using the EQ-5D-5L and cost per life year gained at 1 year and modelled cost per QALY over patient lifetime.

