### Schedule of assessments

Schedule of assessments is detailed in table 1.

**Table 1 T1:** Schedule of assessments

Assessment	Eligibility and randomisation	Baseline	2–7 days (TIPSS arm only)	6 weeks±7 days	6 months±7 days	12 months±7 days
Inclusion criteria*	x					
Exclusion criteria*	x					
Seek informed consent	x					
Relevant medical history taken	x					
Concomitant medication		x		x	x	x
Randomisation	x					
Full blood count		x		x	x	x
TIPSS procedure under fluoroscopic guidance†		x				
Renal function		x		x	x	x
Clotting profile	x			x	x	x
Liver function	x			x	x	x
Diagnostic endoscopy	x					
Standard clinical examination		x		x	x	x
Doppler ultrasound	x		x		x	x
Safety reporting		x	x	x	x	x
Quality of life questionnaires (EQ-5D-5L)		x			x	x
Child-Pugh Score ‡	x				x	x
MELD Score		x			x	x

Color significance HIghlight the assessment variable.

*Refer to text for inclusion and exclusion criteria.

†Early TIPSS arm only.

‡Child-Pugh Score is a minimisation variable.

EQ-5D-5L, EuroQol-5 Dimension-5 Level; MELD, Model For End-Stage Liver Disease; TIPSS, transjugular intrahepatic portosystemic stent–shunt.

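### EQ-5D-5L is left out of the existing 6-week visit, so the QALY for the first 26 weeks must be interpolated from a value around the acute bleed to a 6-month value; adding it is cheap

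*Protocol article*

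**What the plan says.** Three places in the protocol article agree on when utility is measured.

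- Economic evaluation: cost per QALY rests on EQ-5D-5L "estimated using EQ-5D-5L responses at baseline, 6 and 12 months".
- Secondary outcomes: "Health-related quality of life (EQ-5D-5L) at 6 and 12 months post randomisation".
- Schedule of assessments, Table 1: the EQ-5D-5L row is marked at baseline, 6 months and 12 months. The cells for 2–7 days and 6 weeks are empty.

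Table 1 also has a 6-week visit (±7 days) in both arms, with blood tests, clinical examination, concomitant medication and safety reporting. Elsewhere the trial treats 6 weeks as a landmark: it divides early from late rebleeding and is the time of a secondary survival outcome.

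The introduction stresses the early period. It says that "early interventions during the AVB episode are likely to have the greatest impact on outcomes" and describes "each variceal rebleeding episode associated with 20% mortality, particularly in the first 5 days following a bleed". The individual patient data meta-analysis of seven studies that it cites gives survival at 6 weeks and 1 year, early TIPSS versus standard care, as "93% vs 76.8% and 79% vs 62%, respectively, log-rank p<0.001".

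For the analysis, the Economic evaluation section plans multiple imputation for missing cost and outcome data and regression adjustment for baseline imbalance. It leaves detail to a health economics analysis plan and does not name the method for turning EQ-5D-5L values into QALYs.

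**The concern.** The only utility value before 6 months is taken close to the bleed, when patients are acutely ill. The first half-year of QALYs then depends on a path drawn from that value to the one at 6 months. Early TIPSS is placed within 4 days of endoscopy, so recovery from the procedure, early rebleeding and repeat banding all fall inside this gap. If such events make survivors' utility differ between arms at week 6, and the difference has closed by month 6, the planned measurements cannot show it.

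Cost per QALY is a stated outcome, and trial evidence would also feed the lifetime model if that is built. A later analysis plan can choose a different interpolation rule but cannot supply the data. Multiple imputation fills values missing in some participants; it has nothing to work from at a time point observed in none.

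**Working it through.** The article states no QALY figure or precision target, so there is no plan figure to reproduce. The sample size (70 events, 294 participants) comes from the log-rank test on transplant-free survival and does not involve EQ-5D-5L.

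**Inputs from the article:** EQ-5D-5L at weeks 0, 26 and 52; an existing visit at week 6; survival of 93% vs 76.8% at 6 weeks and 79% vs 62% at 1 year (cited meta-analysis); design rates of 60% vs 80% transplant-free at 1 year.

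**Assumed:** area under the curve by trapezoids; all utility values and utility differences; constant hazards where stated.

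**1. Weight on each measurement.** A measurement's weight in years is half the sum of its adjoining intervals, divided by 52.

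| Time point | As planned | With a 6-week measure |
|---|---|---|
| Baseline | 26/2/52 = 0.250 | 6/2/52 = 0.058 |
| 6 weeks | – | (6 + 20)/2/52 = 0.250 |
| 6 months | (26 + 26)/2/52 = 0.500 | (20 + 26)/2/52 = 0.442 |
| 12 months | 26/2/52 = 0.250 | 26/2/52 = 0.250 |

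On the planned schedule the implied utility at week 6 takes 20/26 = 77% of its value from baseline.

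**2. Arm difference at week 6 that closes by month 6.** Let the difference between surviving patients be d at week 6 and zero at weeks 0 and 26. The missed area is a triangle: d × 26/2/52 = 0.25d.

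- d = 0.05: 0.0125 QALY
- d = 0.10: 0.025 QALY
- d = 0.15: 0.0375 QALY

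**3. Recovery curve shared by both arms.** Suppose utility rises from 0.40 to 0.70 by week 6 and stays there.

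- Actual area to week 26: (6 × 0.55 + 20 × 0.70)/52 = 17.3/52 = 0.333
- Straight line from 0.40 to 0.70: (26 × 0.55)/52 = 14.3/52 = 0.275
- Understatement per survivor: 3.0/52 = 0.058

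This cancels between arms except where survival differs. The cited gap at 6 weeks is 93 − 76.8 = 16.2 points, so about 0.058 × 0.162 = 0.009 QALY remains between arms.

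**4. Scale.** Two rough benchmarks for the QALY gain from survival:

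- Design rates with constant hazards: mean event-free time over one year is (1 − S)/(−ln S), giving 0.783 years at 60% and 0.896 at 80%, a difference of 0.113. At utilities of 0.6 to 0.8 that is 0.068 to 0.091 QALY. The amounts in step 2 are then 0.0125/0.091 = 14% to 0.0375/0.068 = 55% of the gain. This benchmark counts transplant-free time, not life years.
- Cited meta-analysis, with the gap rising linearly to 16.2 points at week 6 and then to 17 at week 52: (6/52) × 0.081 + (46/52) × 0.166 = 0.156 life years, or 0.094 to 0.125 QALY. The amounts in step 2 are then 0.0125/0.125 = 10% to 0.0375/0.094 = 40%.

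**The case against.** The strongest reply is that nothing is contradicted. Three sections state one schedule consistently, and the size of the problem comes entirely from assumed utilities. The triangle in step 2 is a constructed scenario. Part of its clinical motivation is also weak on the article's own account: one cited trial and two meta-analyses report no difference, or no significant difference, in hepatic encephalopathy. Early rebleeding, encephalopathy episodes, readmissions and intensive care stays are recorded, so a health economics analysis plan could use them to shape the utility path. All of this stands, and it limits the point to a suggestion for improvement. It does not remove the gap, because recorded events can only inform a modelled path; they do not measure utility at week 6.

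Three stronger readings are tempting and should not be drawn.

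- A reader might infer that utility goes unmeasured just when the arms differ most. The article supports this for survival and rebleeding risk only. In the cited meta-analysis 16.2 of the 17 points of survival gap are present by week 6, but timing of death is followed for the primary outcome and enters the QALY whenever EQ-5D-5L is taken. The article gives no utility data by arm.
- A reader might infer that, because some patients lack capacity at consent, the first half-year rests wholly on imputation. The Consent process section does not say how baseline EQ-5D-5L is completed or that it will be missing. Even if it were missing, an observed 6-month value would carry 0.25 of that period's 0.50 weight.
- A reader might infer a large bias from the shared recovery curve. Step 3 leaves about 0.009 QALY and, if early TIPSS improves survival, the error understates its gain.

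**Conclusion.** The point holds as an inexpensive improvement to the economic outcome. The schedule is certain. Some interpolation over 26 weeks from an acute-illness value is unavoidable, and the missing measurement cannot be restored later. Under the trapezoid rule a 6-week value would cut the baseline weight from 0.25 to 0.058.

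The possible loss is 0.0125 to 0.0375 QALY if survivors' utility differs by 0.05 to 0.15 at week 6 and the difference closes by month 6. That is roughly a tenth to a half of the survival-driven gain, depending on the benchmark. These differences, the utilities and the interpolation rule are all assumptions, and the direction is unknown. The article does not show that such a difference exists, so a biased cost per QALY cannot be claimed, only one exposed to an avoidable gap. Survival, life years, cost per life year gained, the primary outcome and the sample size are untouched.

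**What to change.** Mark EQ-5D-5L at the 6-week visit in Table 1, and amend the Economic evaluation section so that QALYs are computed from baseline, 6 weeks, 6 months and 12 months. Keep 6 and 12 months as the quality-of-life outcome time points.

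For participants already past week 6 and alive then, impute the 6-week value within the multiple imputation already planned, using the values observed in later participants, so that one QALY calculation applies to everyone. Impute separately by arm, otherwise a difference at week 6 would be diluted. Report the three-point calculation as a sensitivity analysis.

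If the questionnaire cannot be added, the health economics analysis plan should pre-specify sensitivity analyses on the shape of the utility path between baseline and 6 months.

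The cost is one more short questionnaire at a visit already scheduled and a minor amendment. The drawback is a mixed schedule, with more of the 6-week data imputed the later the change is made.

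### Lifetime cost per QALY is listed as an outcome without condition, but the model that produces it runs only if the trial shows differences

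*Protocol article*

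**What the plan says.** The lifetime result is stated three times in the protocol article.

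- **Secondary outcomes:** the economic outcomes include "cost per life year gained at 1 year and modelled cost per QALY over patient lifetime". No condition is attached.
- **Economic evaluation, opening sentence:** the evaluation will assess cost-effectiveness by "calculating the cost per life year gained and cost per QALY gained over 12 months and lifetime". Again there is no condition.
- **Economic evaluation, third paragraph:** the lifetime model is introduced by "If there is evidence from the trial that differences between early TIPSS and SOC exist in terms of liver transplantation and mortality", and the sentence continues "as well as other outcomes that may have significant cost or outcome implications beyond the trial period". If that is met, "a Markov model-based economic evaluation will also be conducted over a lifetime time horizon".

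The same third paragraph contains the deterministic and probabilistic sensitivity analyses of the model and the statement "Value of information analysis will also be undertaken to investigate the value of, and the need for, further information on key uncertain model parameters". The second paragraph describes the 12-month within-trial analysis, with bootstrapping, multiple imputation and acceptability curves, and makes none of it conditional. Full details are left to a health economics analysis plan that is not shown.

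**The concern.** An outcome that is listed in advance should be reported whatever the data show. Here the only analysis that can deliver lifetime cost per QALY depends on the results, and the trigger is undefined. The decision whether to report it would thus be taken after the data are known, with room for judgement.

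A decision model with probabilistic sensitivity analysis does not need such a trigger, because it carries the estimated effect together with its uncertainty. A small or imprecise effect is an input to the model and no reason to leave the model out.

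Two things are at stake: the lifetime estimate itself, and the value-of-information analysis. The latter is defined on the parameters of the model, so without the model the article plans none.

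**Working it through.** **Step 1. The statements side by side.**

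| Place in the protocol article | Lifetime cost per QALY | Value of information |
|---|---|---|
| Secondary outcomes | Listed, unconditional | Not mentioned |
| Economic evaluation, opening | Promised, unconditional | Not mentioned |
| Economic evaluation, second paragraph (within-trial) | Not covered; 12 months only | Not mentioned |
| Economic evaluation, third paragraph | Only if the trial gives evidence of differences | Same paragraph, tied to model parameters |

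The first two rows and the last cannot all hold.

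**Step 2. Does the conflict depend on how the trigger is read?** The sentence joins liver transplantation, mortality and other outcomes by *and* and *as well as*. It can be read in two ways.

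- All needed: the model runs only if differences are shown in transplantation, in mortality and in other outcomes.
- Any sufficient: a difference in one of them, for example rebleeding, would do.

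Under both readings, a trial without evidence of any difference yields no lifetime model. The conflict therefore stands either way. The reading changes only how often the model would be skipped.

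**Step 3. The design figures, reproduced first.** The inputs are in the Sample size section: 60% vs 80% at 1 year, HR 0.44, two-sided alpha 0.05, power 90%, attrition 20%, 70 events, 294 participants.

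- HR = ln(0.80)/ln(0.60) = 0.437, which rounds to 0.44.
- Freedman events = (1.960 + 1.282)² × [(1 + 0.44)/(1 − 0.44)]² = 10.51 × 6.61 = 69.5, so 70.
- Mean event probability = (0.40 + 0.20)/2 = 0.30. 70/0.30 = 233.3, so 234 for equal arms.
- 234/(1 − 0.20) = 292.5, so 293, or 294 for equal arms.

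The stated 70 and 294 are reproduced. The evaluable number is 294 × 0.80 = 235.2, about 235.

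**Step 4. An illustrative skip rate.** Assume that evidence means two-sided p<0.05 on transplant-free survival. The article does not say this. With d expected events, Schoenfeld power = Φ(√d/2 × |ln HR| − 1.96), and the skip rate is 1 − power.

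- 60% vs 80%: d = 235/2 × (0.40 + 0.20) = 70.5; HR 0.437; power 0.935; skip rate about 6.5%.
- 60% vs 75%: d = 235/2 × (0.40 + 0.25) = 76.4; HR = ln(0.75)/ln(0.60) = 0.563; power 0.708; skip rate about 29%.

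The design's nominal 90% power corresponds to 1 − 0.90 = 10% in the first case. The difference from 6.5% arises because the plan's events match Freedman's formula, which asks for more events than Schoenfeld's. The 75% in the second case is an assumption, chosen as an effect somewhat smaller than the design effect.

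**The case against.** The strongest reply is that this is a mismatch of wording with limited consequences. The 12-month cost-effectiveness analysis is unconditional and reports decision uncertainty through bootstrapping and acceptability curves. The primary clinical analysis is untouched. Value of information depends on the model by its definition. What counts as evidence is the kind of detail an article leaves to a health economics analysis plan. All of this stands, and it bounds the point. It does not remove the contradiction: an unseen plan could define the trigger, but the article would still promise the lifetime result twice without condition and once with one.

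Some stronger readings are tempting, and the document does not support them.

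- A reader might infer that the condition ignores differences in rebleeding, encephalopathy or cost. The sentence goes on to name other outcomes with longer-term implications. On the looser reading, such a difference could trigger the model.
- A reader might infer that the model is lost exactly when survival is inconclusive, or that it runs only after a favourable result. The text sets no significance threshold and no direction, so evidence of harm would also qualify.
- A reader might infer that the condition biases the modelled effect upward and that removing it cures this. If the trial is significant, an unconditional model would use the same trial estimate. Secondary sources also feed the model.
- A reader might infer that a 12-month horizon alone works against early TIPSS. It cuts off later costs as well as later benefits, so the net direction is unknown.

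**Conclusion.** The concern holds as an internal contradiction with a practical consequence. A listed secondary outcome, together with the probabilistic and value-of-information analyses attached to it, could be reported or dropped according to the results, on an undefined trigger. This rests on the text alone and holds under either reading of the trigger.

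The size cannot be fixed from the document. The skip rates of about 6–7% and 29% are illustrative. They assume a p<0.05 rule, the composite of death and transplantation although the trigger names the two components, and about 235 evaluable participants. That number treats the 20% attrition as contributing no events, whereas the section on missing data keeps such participants until their status is last known. The figures show only that skipping would be uncommon at the design effect and quite possible at a moderately smaller one.

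The point concerns the economic evaluation. It does not affect the validity of the primary comparison or of the 12-month economic analysis.

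**What to change.** Delete the condition in the third paragraph of Economic evaluation. State that the lifetime model, with its probabilistic sensitivity and value-of-information analyses, will be run whatever the trial shows, using the trial estimates with their uncertainty. Add a scenario with no survival difference beyond 12 months, so that a reader can see how far the lifetime result depends on extrapolation. Carry the same wording into the health economics analysis plan.

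If the condition is kept, the least that is needed is to state it in Secondary outcomes and in the opening of Economic evaluation. The trigger should then be defined before results are known: which outcomes, all or any of them, and what counts as evidence. This makes the article consistent but leaves the reporting of the outcome dependent on the results.

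The cost is modelling time that the plan already foresees. No new data are needed.
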